## Abstract

**Background:**

The need for physical cancer rehabilitation programmes (PCRPs), addressing adverse effects from cancer, is growing. Implementing these programmes into daily practice is still a challenge.

Since barriers for successful implementation often arise at different levels in healthcare, multi-faceted strategies focusing on multiple levels are likely more effective than single-faceted strategies. Nevertheless, most studies implementing PCRPs used strategies directed at patients only. The aim of this study is to develop and identify the most effective strategy to implement PCRPs into daily care. We want to assess the added value of a multi-faceted strategy compared with a single-faceted patient-directed strategy.

**Methods/design:**

We will conduct a clustered controlled before and after study (CBA) in the Netherlands that compares two strategies to implement PCRPs. The patient-directed (PD) strategy (five hospitals) will focus on change at the patient level. The multi-faceted (MF) strategy (five hospitals) will focus on change at the patient, professional and organizational levels. Eligibility criteria are as follows: (A) patients: adults; preferably (history of) cancer in the gastro-intestinal, reproductive and/or urological system; successful primary treatment; and without recurrence/metastases. (B) Healthcare professionals: involved in cancer care.

A stepwise approach will be followed:Step 1: Analysis of the current implementation of PCRPs and the examination of barriers and facilitators for implementation, via a qualitative study with patients (four focus groups *n* = 10–12) and their healthcare workers (four focus groups *n* = 10–12 and individual interviews *n* = 30–40) and collecting data on adherence to quality indicators (*n* = 500 patients, 50 per hospital).Step 2: Selection and development of interventions to create a PD and MF strategy during expert roundtable discussions, using the knowledge gained in step 1 and a literature search of the effect of strategies for implementing PCRPs.Step 3: Test and compare both strategies with a clustered CBA (effectiveness, process evaluation and costs), by data extraction from existing registration systems, questionnaires and interviews. For the effectiveness and cost-effectiveness, *n* = 500 patients, 50 per hospital. For the process evaluation, *n* = 50 patients, 5 per hospital, and *n* = 40 healthcare professionals, 4 per hospital. Main outcome measures: % screened patients, % referrals to PCRPs, incremental costs and incremental cost-effectiveness ratios (ICERs).

**Trail registration:**

NCT02205853 (ClinicalTrials.gov)

## Background

The increased incidence of cancer, due to ageing and lifestyle of the western population and the increased survival rate, results in a large group of cancer survivors [1–6]. These patients face unique challenges from persistent adverse effects from their cancer and its treatment [7], which need to be addressed. Cancer and its treatment concerns loss of quality of life (QoL), cancer-related fatigue [8, 9] and other symptoms, such as pain, lymphoedema [10], insomnia and hormone and immune system dysfunctioning [11]. Symptoms depend on the type of cancer, type of treatment and characteristics of the patient and usually emerge before and during treatment and may remain even long after the completion of treatment [12–16]. The prevalence of cancer survivors, who experiencing symptoms of fatigue, is estimated around 20–40 % [8, 17–22]. A lower QoL is experienced by 35 % of the cancer survivors as well [17]. In addition, cancer survivors often have a marked declined cardiopulmonary fitness after finishing their primary treatment [18].

In view of the enormous increase in the number of cancer survivors, it is important to find ways to prevent or mitigate these physical and psychosocial symptoms. In recent years, the positive impact of physical cancer rehabilitation programmes (PCRPs) to counteract both physiologic and psychosocial adverse symptoms in cancer survivors was published [19–28]. Participation in PCRPs has shown to result in decreased fatigue [19, 29–38] and improved cardiopulmonary fitness [29] and QoL [29, 32, 34, 39–44]. Additionally, improvement of muscular strength [45], lean body mass, body fat levels [46], self-esteem and even better chemotherapy completion rates have been reported [47].

PCRPs can be offered in multiple ways (variation in intensity, frequency, duration and format) and at different time points in the cancer trajectory [48]. Regardless of the type of programme, cancer survivors should be stimulated to avoid inactivity and return to normal physical daily activities as soon as possible after surgery, and during adjuvant therapy, related to the WHO health-related physical activity guidelines for the general population [49].

Many experts have concluded that PCRPs are safe during and after cancer (treatment)s, resulting in improvement of many symptoms in cancer survivor groups and that they are probably appropriate to the need of cancer survivors [29, 48, 50–54]. Questionnaires that were rating the experiences of patients with the cancer care in Dutch hospitals showed that the experiences with receiving information and assistance concerning rehabilitation were overall negative. It also showed that patients define information and assistance for referral concerning rehabilitation important aspects of good quality cancer care [55, 56]. Additionally, patients define the information and assistance for referral concerning rehabilitation most suitable for improvement of cancer care in the Dutch healthcare. However, it appears that the uptake of PCRPs is rather low [57–60] and the implementation into daily practice still seems to be a challenge, due to several barriers situated at the patient, provider (hospital) and healthcare system levels [61]. In our experiences, lack of knowledge about effective implementation strategies, but mainly their cost-effectiveness and cost benefits, is a huge barrier on the level of the provider and healthcare systems. On the other hand, competition between providers gives hospitals enough reason to use cost-effective implementation strategies to improve the healthcare service experiences of their patients. A study evaluating the most effective implementation strategy, showing also which aspects of these strategies generate more positive experiences and show cost-effectiveness, might be a catalyst for the implementation of PCRPs.

Studies on implementation of PCRPs are scarce [62–67], but in the last 15 years, over 70 papers on implementing research findings have shed light on the effectiveness of implementation strategies in different aspects of healthcare [68–71]. Various strategies are advocated for the implementation of healthcare innovations, each based on different assumptions and theories on human behaviour and organizations [72–74]. Most theories emphasize that effective implementation cannot take place without a systematic approach and appropriate preparation and planning [75, 76]. Knowledge gained from implementation studies in different aspects of healthcare shows that a tailored implementation strategy should be designed according to the specific features of the innovation, the target group, the setting and the barriers to change. After this, the designed implementation strategy can be tested on effectiveness, feasibility and costs [77, 78] and if needed readjusted.

Since barriers often arise at different levels in the healthcare system, it is very likely that a multi-faceted strategy focusing on different levels (patient, professional and/or the organizational level of care) is more effective than single-faceted strategies [78–81]. Nevertheless, most studies published use single-faceted strategies directed mainly at patients to support the success of implementing PCRPs. Common used patient-directed strategies are patient-empowerment-enhancing tools, often delivered by information and communication technology (ICT). Examples are the use of a website for (1) distribution of educational materials, (2) patient-oriented theoretical feedback based on questionnaires, (3) reminders via e-mail and social media platforms [82] and (4) stimulating monitoring health systems containing heart rate monitors and pedometers [83]. In the process of rehabilitation, empowerment-enhancing tools can have extra value, since confidence to take charge, make decisions and belief in yourself can directly affect the efficacy of the rehabilitation [84]. Sufficient empowerment gives individuals the capacity to influence the behaviour of themselves and others, like the professionals involved in their care [85].

However, strategies aimed at professionals (educational outreach, audit and feedback) can also result in successful implementation (professional performance, patient outcomes and costs) [86, 87]. Strategies directed on the organization could support the implementation of PCRPs as well, mainly because contextual factors, such as workload, poor coordination and management, can be important barriers for success.

In our present study, we aim to identify the most effective strategy to implement PCRPs into daily care. Specific goals are to (1) gain insight into the specific features needed for a successful implementation by exploring the setting and factors (barriers and facilitators) that might influence the implementation of PCRPs. After this, (2) we aim to develop a patient-directed strategy and a multi-faceted strategy. The patient-directed strategy will be designed to embed the success of implementation of PCRPs by influencing the patients, and the multi-faceted strategy will be designed to embed the success by not only influencing the patients but also professionals and organizational aspects. Both strategies will be designed tailored to the setting and found factors affecting implementation. We also aim to (3) compare the effectiveness, experiences of participants (process evaluation) and costs of both strategies on the hospital and patient level and (4) get insight into the additional effects of strategies directed also at professionals and organization aspects compared to patient-only strategies.

Our first hypothesis is that hospitals with a multi-faceted strategy will have a more effective implementation of PCRPs in comparison with hospitals with a patient-directed strategy.

Our second hypothesis is that the patients and professionals will experience more positive experiences with the multi-faceted strategy in comparison with hospitals with a patient-directed strategy.

Our third hypothesis is that those hospitals with the multi-faceted strategy will have higher costs (incremental costs) in comparison with hospitals using the patient-directed strategy.

Our last hypothesis is that the incremental cost-effectiveness ratio (ICER) of the multi-faceted strategy will be lower than the patient-directed strategy.

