The results of the literature search will, together with the knowledge based on the results of the preparatory phase in step 1, be the basis to select and develop the implementation strategies during roundtable discussions. For the five hospitals of the PD-strategy group, a single-faceted patient-directed strategy will be designed that will embed the change only at the patient level. For the hospitals of the MF-strategy group, a multi-faceted strategy will be designed that will embed the change at the patient, professional and organizational levels. The MF strategy will consist also of the PD strategy, so the additional value of the strategies directed at the professional and organization can be evaluated afterwards. For the roundtable discussions, an expert panel will be composed consisting of representatives from the participating hospitals (patients, healthcare professionals and hospital managers), experts on cancer rehabilitation and experts on implementation science.

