### Step 3: testing phase

The designed implementation strategies will be used to deploy the PCRPs in daily care and will be evaluated and compared on (A) effectiveness, (B) experiences of participants (process evaluation) and (C) costs. In all participating hospitals, the trial will be conducted for a half to 1 year, depending on the number of cancer patients per year in the participating hospitals allowing for fast accrual. Between 6 to 12 months after introduction of the implementation strategies, the outcomes of the PD and MF strategies will be evaluated and compared.

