##### Data collection and planned analytic approach

By an ABC approach, we will try to calculate the actual costs and benefits for using the PD- and MF-implementation strategies. In order to accurately assign the costs to the implementation strategies and followed healthcare services, it is necessary to determine exactly the consumption of activities. Afterwards, we need to assign the costs of resources needed to deliver these activities.

The activities and the followed costs of resources (personnel, material and amortization of investment costs) to implement the PCRPs via the PD- or MF-implementation strategies are perceived as the costs, according to ABC approach. On other hand, the prevented activities and their costs of resources that are not used due the implementation of the PCRPs by the PD- or MF-implementation strategies are considered as the benefits. The costs will be measured from the time of preparation and development of strategies until 1 year after the start of the implementation strategies.

Our first step will be to develop protocols of activities performed during the (1) preparation and development of the strategies and (2) activities accumulated by the activity of the healthcare implementation processes (processes of care of patients involved in the implementation processes).

To determine the activities, we will select a sample of patients involved in the implementation process and outline the patient care processes (activities) in each case.

During meetings with professionals from the participating hospitals, we will try to reach a consensus on the protocol of processes (activities) of the PD and MF strategies. The protocol of processes will outline a description of processes and details of their constituent activities.

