Our next step will be to proceed the allocation of resources used in each process. For collecting information on the use of the different elements of the implementation plan by professionals and patients, existing databases will be used as much as possible. When necessary, registration forms will be developed and will be completed by the professionals and the sample of patients involved in the implementation process. The input of resources in the implementation strategy will be assessed by collecting volumes of use of the different elements of the implementation strategy by professionals and patients and multiplying these by the price of each element (market prices, guideline prices or self-determined prices based on costing methods, i.e. full costing). Future costs and effects will be discounted at 4 and 1.5 %, respectively, according to the Dutch guidelines [108].

Cost prices of the processes will be determined using standard unit cost prices according to the Dutch guidelines for costing research [108]. If certain standard unit cost prices are not available, real cost prices will be determined by consulting the management of participating hospitals.

With the protocol of processes of activities and their cost of resources, we will calculate the incremental costs of both the PD and MF strategies. We will also calculate an incremental cost-effectiveness ratio (ICER). The outcomes used for calculating the ICER are the primary outcome measures of our effectiveness study (the ‘To test and compare both implementation strategies in terms of effectiveness’ section): (1) percentage of screened patients and (2) percentage of referrals to PCRPs were needed.

After this, we will compare the expected incremental cost (and potential savings) and cost-effectiveness ratios of the PD with the MF strategy.

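### The planned comparison of one ICER for PD with another for MF does not give the cost of MF's extra effect, which is the study's stated question

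*Protocol article*

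**What the plan says.** The aim is comparative. The abstract's Background states: "We want to assess the added value of a multi-faceted strategy compared with a single-faceted patient-directed strategy". Step 2 nests the strategies so that the added part can be judged later; the sentence begins: "The MF strategy will consist also of the PD strategy, so the additional value of the strategies directed at the professional and organization can be".

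The article's Background section ends with two economic hypotheses. The third is a direct contrast: "those hospitals with the multi-faceted strategy will have higher costs (incremental costs) in comparison with hospitals using the patient-directed strategy". The last gives each strategy its own ratio: "the incremental cost-effectiveness ratio (ICER) of the multi-faceted strategy will be lower than the patient-directed strategy".

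The cost section of Step 3 (Data collection and planned analytic approach) follows the second pattern. It says that "we will calculate the incremental costs of both the PD and MF strategies", adds that an ICER will be calculated on the two primary outcomes, and then that "we will compare the expected incremental cost (and potential savings) and cost-effectiveness ratios of the PD with the MF strategy". The cost Study outcomes section lists ICERs, in the plural, for developing and using PD and MF, and adds a comparison of the two. None of these places names the comparator of an ICER.

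On timing: "The costs will be measured from the time of preparation and development of strategies until 1 year after the start of the implementation strategies". Care activities avoided because of the programmes count as benefits; the reference level against which they are judged avoided is not stated.

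**The concern.** An incremental ratio needs a named alternative: it is the extra cost of one option over another, divided by the extra effect. When one option contains the other, the price of the added part is the difference in cost over the difference in effect between the two. The plan sets up the nesting needed for this, then commits to comparing two separate ratios.

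The abstract lists ICERs among the main outcome measures, and the Background calls missing knowledge of cost-effectiveness a major barrier for providers and healthcare systems. A hospital that already runs, or could run, the patient-directed strategy needs to know what each additional screened or referred patient costs when the professional and organizational elements are added. Two strategy-specific ratios do not tell it. Each of those ratios also depends on the baseline rate, and PD's becomes unstable if PD achieves little.

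**Working it through.** The article gives no cost, ICER or threshold, so there is no figure of the plan's to reproduce. The check is algebra plus an illustration.

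**Inputs.** From Power calculation: 20 % (PD) and 50 % (MF), called effect sizes. Assumed: a common baseline *b* of 0, 5, 10 or 15 % (0 means that 20 and 50 are read as gains), PD cost of 100 per patient, and MF cost of 200, 300 or 400.

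**Formulas.** With effects E_PD = 0.20 − b and E_MF = 0.50 − b:
- PD's own ratio: C_PD / E_PD
- MF's own ratio: C_MF / E_MF
- Price of MF's extra effect: (C_MF − C_PD) / (E_MF − E_PD), whose denominator is 0.30 at every *b*

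**Results**, as cost per additional patient screened or referred:

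| Baseline | MF cost | PD own ratio | MF own ratio | MF versus PD | MF ratio lower? |
|---|---|---|---|---|---|
| 0 % | 200 | 100/0.20 = 500 | 200/0.50 = 400 | 100/0.30 = 333 | yes |
| 0 % | 300 | 500 | 300/0.50 = 600 | 200/0.30 = 667 | no |
| 0 % | 400 | 500 | 400/0.50 = 800 | 300/0.30 = 1000 | no |
| 5 % | 300 | 100/0.15 = 667 | 300/0.45 = 667 | 667 | equal |
| 10 % | 300 | 100/0.10 = 1000 | 300/0.40 = 750 | 667 | yes |
| 15 % | 300 | 100/0.05 = 2000 | 300/0.35 = 857 | 667 | yes |

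**What the planned comparison contains.** MF's own ratio is a weighted average of PD's ratio and the MF-versus-PD ratio, with weights E_PD/E_MF and (E_MF − E_PD)/E_MF. At baseline 0 and MF cost 300: 0.4 × 500 + 0.6 × 667 = 600. So MF's ratio lies below PD's exactly when the MF-versus-PD ratio does, given a common baseline and MF the more effective. The ordering is informative, but the size is lost: 600 stands where 667 is wanted, or 800 where 1000 is wanted.

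**Dependence on baseline.** With MF cost fixed at 300, the hypothesis goes from false to true as the baseline rises from 0 to 15 %, while the price of the extra effect stays at 667. The cost ratio C_MF/C_PD below which the hypothesis holds is E_MF/E_PD: 0.50/0.20 = 2.5 if the figures are gains, and 0.40/0.10 = 4.0 at a 10 % baseline. PD's own ratio rises from 500 to 2000 as its effect shrinks to 5 points.

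**Can the missing ratio be formed?** Yes. The numerator is the contrast in the third hypothesis. The denominator is the between-group difference in pre-post change that the effectiveness analysis already plans. The cost window is the same for both strategies and includes preparation and development.

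**The case against.** The best defence is that this is loose wording. The methods speak of calculating one ICER without naming its comparator, the plural may partly reflect two effect measures, and the third hypothesis already treats incremental cost as MF against PD. If costs and effects are reported by group, any reader can form the MF-versus-PD ratio. The ordering of the separate ratios is also not empty, as shown above. All of this stands, and it limits the point: the result is not lost, but the plan does not commit to reporting it and its hypothesis points to something else.

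Several stronger readings are tempting and are not supported:
- *The cost data start too late to form an increment.* An MF-minus-PD increment needs only both groups' costs over the same window, which the article provides. The cost of delivering a strategy before its preparation starts is zero.
- *Costs and effects cover incompatible periods.* The article says that "the trial will be conducted for a half to 1 year, depending on the number of cancer patients per year in the participating hospitals", and separately sets evaluation at 6 to 12 months. Hospital volume is tied to trial length, and the effects are percentages, not totals that build up with time. This does not invalidate the ratio.
- *Savings cannot be observed.* The reference is unstated, but the cost section uses existing databases as far as possible, and Step 1 already retrieves pre-measurement indicator data retrospectively from registration systems.
- *Methods for uncertainty in the ratio are missing.* That is analysis-plan detail and no finding here.

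**Conclusion.** The concern holds in a limited form. The last hypothesis and the cost analysis compare two strategy-specific ratios with no comparator named, whereas the aim and the nested design call for the cost of MF's extra effect over PD. Followed as written, the plan answers at most whether that extra effect is cheaper per unit than PD's own, and the answer moves with the baseline.

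The size cannot be read from the article. Under the assumed costs, the price of the extra effect runs from 333 to 1000 per additional patient, against MF ratios of 400 to 800 at baseline 0. Those figures, and the 2.5 threshold, rest on invented costs and on reading 20 % and 50 % as gains. A reader might infer that the planned comparison is meaningless or would mislead in a known direction; the algebra does not support that. The primary effectiveness outcomes and their comparison are unaffected.

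A narrower second point also holds: the avoided activities counted as benefits have no stated pre-implementation reference, although effects are measured before and during implementation.

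**What to change.** 1. In the last hypothesis and in the cost sections (Data collection and planned analytic approach; Study outcomes), make the main ratio, for each of the two primary outcomes: (mean cost MF − mean cost PD) / (pre-post effect MF − pre-post effect PD).
2. Name the comparator of every ICER. Any strategy-specific ratio should be stated as against the pre-measurement and labelled secondary.
3. For avoided activities, choose one of two routes and say which. Either take reference care use for the pre-measurement patients from the existing registration systems, or limit savings to the MF-minus-PD difference within the cost window. The second needs no new data, but in this non-randomised comparison it leaves the cost difference unadjusted for baseline costs.

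Items 1 and 2 are rewording only, and the cost window can stay as it is. Item 3 needs at most a small additional extraction. No new patients or procedures are involved. Trial status reports that indicator data had not been gathered at submission, so the change could be made beforehand.
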